**Table 4: Guidelines for Managing Atezolizumab-Associated Endocrine Toxicity**

| Severity                                                       | Management                                                                                                                                                                                                                                                                                                                                                                                                                                                                                                                                                               |
|----------------------------------------------------------------|--------------------------------------------------------------------------------------------------------------------------------------------------------------------------------------------------------------------------------------------------------------------------------------------------------------------------------------------------------------------------------------------------------------------------------------------------------------------------------------------------------------------------------------------------------------------------|
| Asymptomatic Hypothyroidism                             | 
 
Continue atezolizumab.
 
Start thyroid replacement hormone.
 
Monitor TSH weekly.
 
                                                                                                                                                                                                                                                                                                                                                                                                                        |
| Symptomatic Hypothyroidism                              | 
 
Hold atezolizumab.
 
Start thyroid replacement hormone therapy
 
Consider referral to an endocrinologist.
 
Restart atezolizumab when symptoms are controlled by thyroid replacement and TSH levels are decreasing.
 
                                                                                                                                                                                                                                                                               |
| Asymptomatic Hyperthyroidism                            | 
 
If serum TSH < 0.5 mU/l, repeat with free T4 and T3 to diagnose asymptomatic hyperthyroidism
 
If confirmed, and in the absence of symptoms, continue atezolizumab and repeat tests in 4 weeks.
 
If thyroid values remain stable and patient is asymptomatic, follow labs monthly
 
Hold atezolizumab if TSH < 0.1 mU/l or if patient develops symptomatic hyperthyroidism
 
Consider referral to an endocrinologist and treat according to symptomatic hyperthyroidism guidelines.
 
 |
| Symptomatic Hyperthyroidism                             | 
 
Hold atezolizumab
 
Start beta-blockers, eventually methimazole as needed
 
Consider referral to an endocrinologist
 
Restart atezolizumab when symptoms are controlled by therapy
 
Permanently discontinue atezolizumab for life threatening immune related hyperthyroidism
 
                                                                                                                                                                                                              |
| Symptomatic panhypopituitarism and any grade 3-4 events | 
 
Hold atezolizumab
 
Consult endocrinologist
 
Perform appropriate imaging
 
Treat with an initial dose of methylprednisolone 1 to 2 mg/kg per day intravenously followed by oral prednisone 1 to 2 mg/kg per day
 
Taper steroids when symptoms improve to G0 or G1. Taper over > 1 month.
 
Restart atezolizumab when symptoms are controlled by therapy
 
                                                                                                                        |

TSH = thyroid-stimulating hormone; T4 = thyroxine

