- For patients with Grade 2 AST/ALT, and/or alkaline phosphatase abnormality at baseline, an increase to  $\geq 10 \times$  the upper limit of normal (ULN) that does not resolve to Grade  $\leq 2$  within 48 hours (if symptomatic) or that does not resolve to Grade  $\leq 1$  within 3 weeks of onset (if asymptomatic) will be considered a DLT after AST/ALT elevation due to disease progression has been ruled out
- Grade  $\geq 3$  pneumonitis
- Grade  $\geq 3$  colitis

Failure to recover from any toxicity that results in a delay of 2 scheduled administrations of atezolizumab is considered a DLT. The following are not considered DLTs:

- Grade  $\geq 3$  nausea, vomiting, or diarrhea that resolves to Grade  $\leq 1$  with or without treatment prior to the next infusion

- Grade  $\geq 3$  immune-related adverse event that resolves to Grade  $\leq 1$  with immunosuppressant therapy within 3 weeks of its onset
- Grade  $\geq 3$  fatigue that resolves to Grade  $\leq 2$  within 1 week
- Grade  $\geq 3$  arthralgia that can be adequately managed with supportive care or that resolves to Grade  $\leq 2$  within 1 week
- Grade  $\geq 3$  hypophosphatemia reversible to  $<$  Grade 2 within 1 week
- Grade  $\geq 3$  laboratory abnormality that is asymptomatic and deemed by the investigator not to be clinically significant
- Grade  $\geq 3$  autoimmune thyroiditis or other endocrine abnormality that can be managed by endocrine therapy or hormonal replacement
- Grade  $\geq 3$  tumor flare defined as local pain, irritation, or rash localized at sites of known or suspected tumor
- Alopecia (any grade)
- Infusion related reactions (IRRs): IRRs are not considered to be DLTs because based on experience with monoclonal antibodies; IRRs are not dose-related events. Precautions will be taken if IRRs Grade  $\geq 2$  occurs. If described precautions are not sufficient, other options will be discussed between the sponsor and the investigator.

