#### **6.3.1 Atezolizumab dose modification and management of specific adverse events**

There will be no dose reduction for atezolizumab in this study. Patients may temporarily suspend study treatment if they experience an adverse event that requires a dose to be held. If atezolizumab is held because of adverse events for  $> 42$  days beyond the last dose, then the patient will be discontinued from atezolizumab treatment and will be followed for safety. If, in the judgment of the investigator, the patient is likely to derive clinical benefit from resuming atezolizumab after a hold  $> 42$  days, study drug may be restarted with the approval of the PI.

If a patient must be tapered off steroids used to treat adverse events, atezolizumab may be held for  $> 42$  days until steroids are discontinued or reduced to prednisone dose (or dose equivalent)  $\leq 10\text{mg/day}$ . The acceptable length of interruption will depend on agreement between the investigator and the PI.

Dose interruptions for reason(s) other than adverse events, such as surgical procedures, may be allowed by PI approval. The acceptable length of interruption will depend on agreement between the investigator and the PI.

Toxicities associated or possibly associated with atezolizumab treatment should be managed according to standard medical practice. Additional tests, such as autoimmune serology or biopsies, may be used to determine the etiology. Discontinuation of atezolizumab may not have an immediate therapeutic effect and, in severe cases, immune-mediated toxicities may require acute management with topical corticosteroids, systemic corticosteroids, mycophenolate, TNF $\alpha$  inhibitors, or tacrolimus. Further administration of atezolizumab will depend on whether the potential benefits of therapy outweigh the potential risks. Atezolizumab should be permanently discontinued in patients with life-threatening, immune-mediated adverse events. The following sections provide guidance for handling specific adverse events.

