### 6.3.1.4 Endocrine toxicity

Thyroid disorders, hypophysitis and adrenal insufficiency have been associated with the administration of atezolizumab. Patients with unexplained symptoms such as fatigue, myalgias, impotence, mental status changes, or constipation should be investigated for the presence of thyroid, pituitary, or adrenal endocrinopathies, as well as for hyponatremia or hyperkalemia. An endocrinologist should be consulted if an endocrinopathy is suspected. TSH and free T4 levels should be obtained to determine whether thyroid abnormalities are present. TSH, prolactin, and a morning cortisol level will help to differentiate primary adrenal insufficiency from primary pituitary insufficiency. Endocrine toxicity should be managed according to the guidelines in Table 4.

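### Table 4 places a grade 3-4 symptomatic thyroid event under two rows that disagree on systemic steroids and, if hyperthyroidism is life-threatening, on whether atezolizumab may be restarted

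*Protocol*

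**What the plan says.** Section 6.3.1.4 names thyroid disorders, hypophysitis and adrenal insufficiency, and then directs: "Endocrine toxicity should be managed according to the guidelines in Table 4". Table 4 has five rows. Four concern the thyroid and are defined by direction (hypo- or hyperthyroidism) and by presence of symptoms. None of the four mentions a grade.

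- Symptomatic Hypothyroidism: hold atezolizumab and give hormone replacement. The restart line reads "Restart atezolizumab when symptoms are controlled by thyroid replacement and TSH levels are decreasing".
- Symptomatic Hyperthyroidism: hold, give beta-blockers with methimazole if needed, and restart on symptom control. It adds: "Permanently discontinue atezolizumab for life threatening immune related hyperthyroidism".
- The last row is headed "Symptomatic panhypopituitarism and any grade 3-4 events". After hold, endocrinology consult and imaging it says: "Treat with an initial dose of methylprednisolone 1 to 2 mg/kg per day intravenously followed by oral prednisone 1 to 2 mg/kg per day". The steroids are tapered over more than one month once symptoms reach grade 0 or 1. It ends: "Restart atezolizumab when symptoms are controlled by therapy".

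Section 6.3.1, which introduces all the toxicity tables, separately requires permanent discontinuation for immune-mediated events that are life-threatening.

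**The concern.** The last row is defined by grade and the thyroid rows by symptoms, so the two definitions cross. A grade 3 or 4 symptomatic thyroid event meets both. The notes under the table only expand abbreviations, and no text ranks the rows.

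The trial runs at several centres. Two of them, each following the table, could treat the same grade 3 thyroid event either without any systemic steroid or with a weight-based steroid course. After life-threatening hyperthyroidism, one could stop atezolizumab permanently while the other restarts it. What is at stake is the safety of the individual patient and uniform conduct across sites.

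**Working it through.** No statistical figure in the protocol depends on this point, so the check compares the rows with each other and with the rest of section 6.3.1.

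**Step 1: do the rows overlap?** Table 4 governs all endocrine toxicity, thyroid disorders included. The symptomatic thyroid rows have no upper grade. The last row takes in *any* grade 3-4 event and does not exclude thyroid events. The overlap is every symptomatic thyroid event of grade 3 or 4.

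**Step 2: what does each row order in the overlap?**

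| Event | Thyroid row | Last row | Agreement |
|---|---|---|---|
| Grade 3 hypothyroidism, symptomatic | Hold; hormone replacement; no steroid; restart on symptom control with falling TSH | Hold; steroid 1 to 2 mg/kg/day, then taper over more than 1 month; restart on symptom control | Hold and restart broadly agree; steroid differs |
| Grade 3 hyperthyroidism, symptomatic | Hold; beta-blocker, methimazole if needed; no steroid; restart on symptom control | As above | Hold and restart agree; steroid differs |
| Life-threatening hyperthyroidism | Permanent discontinuation | Hold; steroid; restart on symptom control, no exception | Direct contradiction |

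**Step 3: is the last case really inside the last row?** The row names grade 4. Treating a grade 4 event as life-threatening is an assumption here, but it matches the protocol's usage: the Grade 4 row of Table 3 (dermatologic toxicity) is the one that orders permanent discontinuation for a life-threatening event. On that footing the last row also runs against the general rule in section 6.3.1.

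**Step 4: restart after steroids.** The restart rules in Table 2 (hepatotoxicity, grades 2 and 3), Table 3 (grade 3), Table 5 (grade 2) and Table 6 (grade 3-4 enzyme rises and autoimmune pancreatitis) all require a prednisone equivalent of 10 mg/day or less. Table 4's last row orders systemic steroids but gives no level, so restart on symptom control alone complies with that row.

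**Step 5: scale of the steroid difference.** The protocol gives no body weight. Assuming 60 to 80 kg, the pre-taper dose is 1 mg/kg x 60 kg = 60 mg/day up to 2 mg/kg x 80 kg = 160 mg/day, against 0 mg/day in the thyroid rows. This is the dose before tapering. The month or more refers to the taper, during which the dose falls.

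**The case against.** The strongest reply is that the table can be read sensibly as it stands. Its first column is headed Severity, so the last row may be a further tier added to the thyroid treatment. Nothing in it forbids beta-blockers or replacement hormone. Alternatively, the pairing with panhypopituitarism and imaging suggests a row meant for pituitary events. Both readings are possible, but the protocol states neither, and they lead to different treatment. The pituitary reading also leaves grade 3-4 adrenal insufficiency, which section 6.3.1.4 names, without a row.

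A second reply is that the general rule in section 6.3.1 already covers life-threatening events. It may indicate how the sponsor would resolve the conflict. It does not remove the last row's unqualified restart line, and no text says that the general rule overrides the table.

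A third reply is that these events will be rare. Section 6.1.1 lists the most frequent related grade 3 events among 412 monotherapy patients, down to 3 patients (0.7%), and no thyroid event appears. At that rate 40 patients would yield 40 x 3/412 = about 0.3 events. The list is not exhaustive and does not concern this combination, but the point is fair: the conflict may arise seldom. That limits how often it bites, not whether it exists.

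On steroid level, Table 10 (myositis) also allows resumption after corticosteroids without a stated level, so Table 4 is not alone. The comparison with Tables 2, 3, 5 and 6 shows a gap to be clarified, not a contradiction.

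Some stronger inferences do not hold:

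- A reader might take section 6.3.1 to set 10 mg/day as a binding condition for resuming. The text permits a hold beyond 42 days while steroids are tapered to that level, with the length agreed between the investigator and the principal investigator.
- A reader might take section 4.2 as prescribing treatment without steroids. Its reference to "autoimmune thyroiditis or other endocrine abnormality that can be managed by endocrine therapy or hormonal replacement" is an exception for counting dose-limiting toxicities, conditional on such management being possible.
- A reader might think that every thyroid row stops the drug when an event is life-threatening. Only the Symptomatic Hyperthyroidism row does.

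**Conclusion.** The inconsistency stands and should be corrected. A grade 3-4 symptomatic thyroid event falls under two rows of Table 4 that differ on systemic steroids, with no rule of precedence. At grade 3 the disagreement is confined essentially to the steroid instruction. For life-threatening hyperthyroidism it extends to permanent stop against restart, where the last row conflicts with both the hyperthyroidism row and section 6.3.1. The missing steroid level for restart is a lesser gap in the same row.

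The conclusion rests on the table's literal wording and, for the stop-versus-restart conflict, on reading grade 4 as including life-threatening events.

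A reader might go further and infer bias in the primary result, since one patient is 1/40 = 2.5 percentage points of the final proportion. That arithmetic is true of any patient. The protocol gives no frequency for these events and no link from their management to progression status at 6 months, so no effect on the primary endpoint, type I error or power is shown or claimed.

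**What to change.** Reword Table 4 so that each grade 3-4 endocrine event falls under exactly one row, or add a line stating which row takes precedence. In particular, state which events the last row's grade 3-4 wording covers, and limit the thyroid rows to match.

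Reconcile the last row's restart line with the permanent stop in the hyperthyroidism row and with the general rule in section 6.3.1, and state whether a steroid level applies before restart. Which management applies to which event is for the sponsor to decide.

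The cost is a wording change to one table by amendment, with no new assessments and no change to sample size or analysis.

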### 6.3.1.5 Pulmonary toxicity

Dysnea, cough, fatigue, hypoxia, and pulmonary infiltrates have been associated with the administration of atezolizumab and have primarily been observed in patients with underlying NSCLC.

Appropriate workup for pulmonary adverse events should include the following as appropriate, as well as ruling out alternative causes (e.g., lymphangitic carcinomatosis, infection, heart failure, or chronic obstructive pulmonary disease or pulmonary hypertension):

- Measurement of oxygen saturation (i.e., arterial blood gas)
- High-resolution CT scan of the chest
- Bronchoscopy with bronchoalveolar lavage and biopsy
- Pulmonary function tests (with diffusion capacity of the lung for carbon monoxide)

Pulmonary function testing and CT with a pulmonary embolism protocol may also be helpful in the diagnostic evaluation. For patients with clinical symptoms, treatment should include administration of corticosteroids and/or oxygen when indicated. Consultation with a pulmonologist is appropriate for a suspected lung immune-related adverse event, and a bronchoscopy with biopsy should be performed, unless contraindicated, prior to the administration of corticosteroids.

Patients will be assessed for pulmonary signs and symptoms throughout the study. Pulmonary toxicity should be managed according to the guidelines in Table 5.

**Table 5: Guidelines for Managing Atezolizumab-Associated Pulmonary Toxicity**

| Pulmonary Toxicity   | Management                                                                                                                                                                                                                                                                                                                                                                                                                                                                                                                                                                                                                                 |
|----------------------|--------------------------------------------------------------------------------------------------------------------------------------------------------------------------------------------------------------------------------------------------------------------------------------------------------------------------------------------------------------------------------------------------------------------------------------------------------------------------------------------------------------------------------------------------------------------------------------------------------------------------------------------|
| Grade 1       | 
 
• May continue atezolizumab with close monitoring
 
• Re-evaluate on serial imaging
 
• Consider consultation of pulmonologist
 
                                                                                                                                                                                                                                                                                                                                                                                                                                             |
| Grade 2       | 
 
• Hold atezolizumab.
 
• Consult a pulmonologist; investigate for other etiologies and consider bronchoscopy/BAL.
 
• If bronchoscopy is consistent with immune-related etiology, start 60 mg prednisone equivalent per day
 
• When improves to G0 or G1, then taper steroids over <math>\geq 1</math> month
 
• Atezolizumab may be resumed if the event improves to G0 or 1 within 12 weeks and corticosteroids have been reduced to the equivalent of oral prednisone 10 mg daily or less.
 
• Treat as G3/4 if recurrent episode of pneumonitis.
 
 |
| Grade 3 and 4 | 
 
• Permanently discontinue atezolizumab
 
• Consult a pulmonologist; investigate for other etiologies and bronchoscopy/BAL is recommended.
 
• Start 60 mg prednisone equivalent per day
 
• When improves to G0 or G1, then taper steroids over <math>\geq 1</math> month
 
• If not improving after 48 hrs or worsening: add additional immunosuppression (e.g. infliximab, iv immunoglobuline, or mycophenolate mofetil)
 
• Contact PI if atezolizumab is discontinued.
 
                                                                            |

### 6.3.1.6 Pancreatic toxicity

Symptoms of abdominal pain associated with elevations of amylase and lipase suggestive of pancreatitis have been associated with the administration of other immunomodulatory agents. The differential diagnosis of acute abdominal pain should include pancreatitis. Appropriate workup should include an evaluation for obstruction, as well as serum amylase and lipase tests. Pancreatic toxicity should be managed according to the guidelines in Table 6.

**Table 6. Guidelines for Managing Atezolizumab-Associated Pancreatic Toxicity**

| Amylase/Lipase Abnormalities                                                                  | Management                                                                                                                                                                                                                                                                                                                                                                                                                                                                                                                                                                                                                                                               |
|-----------------------------------------------------------------------------------------------|--------------------------------------------------------------------------------------------------------------------------------------------------------------------------------------------------------------------------------------------------------------------------------------------------------------------------------------------------------------------------------------------------------------------------------------------------------------------------------------------------------------------------------------------------------------------------------------------------------------------------------------------------------------------------|
| Grade 1
Amylase/lipase ( $>ULN$ and $\leq 2 \times ULN$ ) and asymptomatic          | 
 
Continue atezolizumab.
 
Monitor amylase/lipase levels prior to dosing.
 
                                                                                                                                                                                                                                                                                                                                                                                                                                                                                                                                         |
| Grade 2
Amylase/lipase ( $> 2 \times ULN$ to $\leq 5 \times ULN$ ) and asymptomatic | 
 
Continue atezolizumab.
 
Monitor amylase/lipase weekly.
 
                                                                                                                                                                                                                                                                                                                                                                                                                                                                                                                                                         |
| Grade 3 and 4
Amylase/lipase ( $> 5 \times ULN$ ) and asymptomatic                  | 
 
Hold atezolizumab.
 
Consult a gastroenterologist
 
Monitor amylase/lipase every other day and only consider oral prednisone 60 mg daily or equivalent if symptoms start to occur,
 
When lab abnormalities return to G0 or G1, then taper steroids over <math>\geq 1</math> month
 
Atezolizumab may be resumed if the event resolves to G0 or G1 within 12 weeks and corticosteroids have been reduced to the equivalent of oral prednisone 10 mg daily or less
 
Permanently discontinue atezolizumab for recurrent symptomatic grade 3 or 4 amylase/lipase
 
                      |
| Autoimmune pancreatitis (abdominal pain and raised amylase/lipase levels)              | 
 
Hold atezolizumab.
 
Consult a gastroenterologist.
 
Administer IV steroids (prednisone equivalent of 60 mg/day) and convert to oral steroids when symptoms improve.
 
When symptoms and lab abnormalities improves to G0 or G1, then taper steroids over <math>\geq 1</math> month
 
Atezolizumab may be resumed if the event improves to G0 or G1 within 12 weeks and corticosteroids have been reduced to the equivalent of prednisone 10 mg po daily or less
 
Permanently discontinue atezolizumab for life-threatening immune-related pancreatitis or recurrent pancreatitis.
 
 |

IV = intravenous; ULN = upper limit of normal.

